## Abstract

**Background:**

Head and neck cancer patients undergoing concomitant chemoradiotherapy (CCRT) frequently experience loss of muscle mass and reduced functional performance. Positive effects of exercise training are reported for many cancer types but biological mechanisms need further elucidation. This randomized study investigates whether progressive resistance training (PRT) may attenuate loss of muscle mass and functional performance. Furthermore, biochemical markers and muscle biopsies will be investigated trying to link biological mechanisms to training effects.

**Methods:**

At the Departments of Oncology at Herlev and Aarhus University Hospitals, patients with stage III/IV squamous cell carcinoma of the head and neck, scheduled for CCRT are randomized 1:1 to either a 12-week PRT program or control group, both with 1 year follow-up. Planned enrollment is 72 patients, and stratification variables are study site, sex, p16-status, and body mass index. Primary endpoint is difference in change in lean body mass (LBM) after 12 weeks of PRT, assessed by dual-energy X-ray absorptiometry (DXA). The hypothesis is that 12 weeks of PRT can attenuate the loss of LBM by at least 25%. Secondary endpoints include training adherence, changes in body composition, muscle strength, functional performance, weight, adverse events, dietary intake, self-reported physical activity, quality of life, labor market affiliation, blood biochemistry, plasma cytokine concentrations, NK-cell frequency in blood, sarcomeric protein content in muscles, as well as muscle fiber type and fiber size in muscle biopsies. Muscle biopsies are optional.

**Discussion:**

This randomized study investigates the impact of a 12-week progressive resistance training program on lean body mass and several other physiological endpoints, as well as impact on adverse events and quality of life. Furthermore, a translational approach is integrated with extensive biological sampling and exploration into cytokines and mechanisms involved. The current paper discusses decisions and methods behind exercise in head and neck cancer patients undergoing concomitant chemoradiotherapy.

**Trial registration:**

Approved by the Regional Ethics Committee for the Capital Region of Denmark (protocol id: H-15003725) and registered retrospectively at ClinicalTrials.gov (NCT02557529) September 11th 2015.

**Electronic supplementary material:**

The online version of this article (doi:10.1186/s12885-017-3388-0) contains supplementary material, which is available to authorized users.

## Background

Patients with locally advanced head and neck squamous cell carcinoma (HNSCC) undergoing concomitant chemoradiotherapy (CCRT) are often subjected to severe treatment side effects which may lead to weight loss, including loss of lean body mass, negatively impacting physical function and maybe even treatment outcome [1–7]. The loss of lean body mass (LBM) during treatment is likely to be multifactorial and HNSCC patients are particularly susceptible for several reasons: Cancer disease per se can cause muscle wasting [8, 9]; along with cisplatin chemotherapy [10, 11] and prednisolone [12, 13], which is often used as antiemetic treatment. Furthermore, many HNSCC patients fail to maintain sufficient energy and protein intake for a period of time [14, 15] due to treatment side effects, e.g. mucositis, dry mouth, pain, and fatigue. This may render patients in a catabolic state, a condition that inevitably will lead to further loss of muscle mass [16] as muscles are the largest and primary protein and energy reserve of the body. Interestingly, it has been shown that patients fail to maintain weight and LBM despite sufficient dietary intake [14], hence other interventions with potential to attenuate muscle wasting in HNSCC patients during treatment are needed.

In a preclinical study voluntary exercise efficiently mitigated cisplatin-induced muscle wasting [17]. Specifically, progressive resistance training (PRT) induces muscle hypertrophy in both healthy adults and cancer patients and definitely holds the potential to counteract cancer-related muscle wasting, too [8, 18, 19]. Twelve weeks of PRT after radiotherapy has been shown to rebuild LBM in HNSCC patients [20, 21], hence, PRT could be a meaningful approach for LBM preservation during treatment.

In a pilot study of a 12-week supervised PRT program during CCRT at our facility, we found that the intervention was feasible and appreciated by patients ([name] et al., manuscript submitted). Knowing this, the present randomized trial is launched to investigate whether PRT during CCRT has a clinically relevant advantage, in terms of attenuated loss of LBM, compared with a control group not offered any structured training. In addition, extensive biological sampling is incorporated in this study adopting a translational approach, with the aim of exploring not only *if* it works, but also contributing to questions of *how* and *why*.

There is an echoing lack in clinical studies investigating the biological mechanisms. Preclinical studies demonstrate a direct inhibitory effect on cancer growth through different mechanisms [22–26]. One very plausible mechanism being exercise-mediated induction of intratumoral natural killer cells (NK cells) [27], unequivocally linking exercise to attenuation of tumor growth in mice [28, 29].

Exercise in its broadest sense is a very heterogeneous activity making the description of exercise interventions in clinical trials critical [30]. This article describes the study design of a 12-week progressive resistance training program in head and neck cancer patients undergoing concomitant chemoradiotherapy, sharing thoughts behind the decision making.

## Methods/design

### Design

In this prospective phase II multi-center randomized study in patients with HNSCC scheduled for radiotherapy concomitant with chemotherapy (cisplatin), the effects of 12-week PRT are investigated. The study is planned to include 72 patients from the departments of oncology at Aarhus and Herlev Hospitals in Denmark, see study flow in Fig. 1. Also, a third center was opted to participate but this site will not be including patients due to capacity issues.

**Fig. 1 Fig1:**
[figure not shown]
Overall study design

Ethics approval has been obtained from the regional Ethics Committee for the Capital Region of Denmark (H-15003725) and the Danish Data Protection Agency (HGH-2015-003; 2005–41-4802; 2014–41-3510). The study is registered at clinicaltrials.gov (NCT02557529) September 11th 2015. This article describes protocol version 4.0 from April 1st 2016.

The manuscript applies to the SPIRIT guidelines of randomized trials. The SPIRIT checklist, appendix for the SPIRIT checklist, as well as the World Health Organization (WHO) Trial Registration Data Set can be found in additional files 1, 2 and 3.

### Participants

Patients are eligible if the following inclusion criteria are fulfilled: 1) Histologically verified primary head and neck squamous cell carcinoma (HNSCC) of the oral cavity, oropharynx, hypopharynx, larynx, or in lymph nodes of the neck from an unknown primary tumor; 2) candidate for curatively intended CCRT (weekly cisplatin during radiotherapy, 66–68 Gy) according to Danish Head and Neck Cancer (DAHANCA) group (i.e. patients with stage III-IV disease, www.dahanca.dk) [31]; 3) performance status (PS) 0–1 (Eastern Cooperative Oncology Group Performance (ECOG); 4) age ≥ 18 years; 5) signed informed consent.

Exclusion criteria are: 1) Body Mass Index (BMI) < 20.5; 2) comorbidity potentially interfering with attendance or test results, e.g. other cancers, diabetes, prednisolone treatment); 3) tonsillectomy within 1 week before inclusion; 4) psychological, social or geographical conditions that could influence protocol adherence; 5) insufficient bone marrow function (hemoglobin <6 mmol/L, leucocytes <2.5 × 10^9^/L, or thrombocytes <50 × 10^9^/L; 6) diastolic blood pressure < 45 or >95, resting heart rate > 100; 7) signs of ischemia on electrocardiogram; 8) pregnancy.

### Randomization

Patients will be stratified by site (Herlev/Aarhus), sex (male/female), p16-status of the tumor (positive/negative) and BMI (<30/≥30) and randomized 1:1 to either a training group performing a 12-week PRT program or control group. If a patient leaves the study within the first week, the number of patients randomized will be increased by one. Patient inclusion form is faxed to The Danish Head and Neck Cancer (DAHANCA, Aarhus, Denmark) group administration, that performs the randomization using a software randomization file (developed and used by the DAHANCA group) that automatically and randomly allocates each patient in either group. The personnel conducting the randomization are independent of clinical personnel and are not otherwise involved in the study.

### Treatment

All patients will receive curatively intended CCRT, 66 to 68 Gy, in 2 Gy fractions, 6 fractions/week, with concurrent nimorazole perorally (1200 mg/m^2^) [32] before each fraction (1000 mg/m^2^ for same day second fraction), and weekly cisplatin (40 mg/m^2^, max. 70 mg). Prophylactic antiemetics are administered according to institutional guidelines (Additional file 4: Table S1).

### Intervention

The PRT program comprises seven conventional resistance training exercises targeting the large muscle groups of the body (chest press, low row (Herlev site)/lateral pull down (Aarhus site), hamstring curls, knee extension, leg press, abdominal crunches (Herlev site)/sit ups (Aarhus site), back extensions) (Additional file 5: Figure S1). The latter two included primarily to ensure a full body workout. The training protocol (Table 1) was tested in our pilot study ([name] et al., manuscript submitted) and is almost identical to the protocol developed and used in the DAHANCA 25 trials [20, 21]. The first week is an introductory week with high repetition number and low load, as many HNSCC patients are resistance training naïve. The intensity and volume progressed throughout the program from two to three sets with a load corresponding to 15 to 8 repetition maximum (RM), i.e. the load that can be lifted respectively 15 to 8 times using proper technique (See Tables 1 and 2). This progression model is in accordance with the guidelines from the American College of Sports Medicine (ACSM) [33]. Due to the focus on muscular hypertrophy, patients are urged to perform all sets in all exercises to exhaustion within the given RM target, thereby ensuring local muscular fatigue. In accordance, patients are instructed to perform all sets of each exercise before moving on to the next exercise and also to perform the lower body exercises after each other before moving to upper body exercises. Each exercise is executed in full range of motion and with rest periods of no more than 60 s between sets (Table 2). If more repetitions than planned can be performed, the training load will be increased to match the specific RM target. Training sessions are planned three times a week every other day ensuring optimal recovery time for maximal hypertrophic response. In case of temporary discontinuation, patients will proceed with the same weight as when they paused, but will be adjusted to ensure the proper RM target is reached.

**Table 1 Tab1:** Exercise progression model

Training session	Repetitions	Sets
1–3	15	2
4–6	12	2
7–18	12	3
19–31	10	3
32–36	8	3

**Table 2 Tab2:** Description of the PRT program

Load	15 RM (week 1), 12 RM (week 2–6), 10 RM (week 7–10), 8 RM (week 11–12)
Repetitions	15 (week 1), 12 (week 2–6), 10 (week 7–10), 8 (week 11–12)
Sets per sessions	2 (week 1–2), 3 (week 3–12)
Sessions per week	3
Duration of training period	12 weeks
Rest between sets	45–60 s
Rest between repetitions	0 s
Range of motion	Maximum possible
Rest between training sessions	Training every other day

Abbreviations: *PRT* progressive resistance training, *RM* repetition maximum, e.g. 15 RM is the heaviest load that can be lifted 15 times using proper technique. Sec, seconds

The PRT program starts concurrently with CCRT. 36 training sessions are planned, i.e. thrice weekly for 12 weeks, thus continuing approximately 6 weeks further than CCRT. If a session is cancelled due to treatment related interventions, radiotherapy, scans, or due to public holidays, the session will be replaced at the end of the training program. Sessions missed for personal reasons or incapacitation will not be substituted. It will be ensured that the PRT program and tests never compromise treatment schedule.

At the Herlev site conventional exercise equipment is used for all exercises but due to different equipment available at the involved sites, three specific exercises differ but with only minimal difference in target muscle groups or progression options. Thus, at the Aarhus site sit-ups will be performed as traditional floor exercises with free weights ensuring possible progression in intensity. Hamstring curls will be performed using elastic bands (TheraBand, The Hygenic Corporation, Ohio, USA) with varying resistance and lateral pull down replaces low seated row in Aarhus. Conventional resistance training machines (Technogym, Gambettola, Italy) are used at both sites.

During the first 6 weeks all training sessions are supervised by physiotherapist or educated training instructors. When possible the same supervised training modality at the hospital training facility will continue for the remaining 6 weeks. If a patient is unable to attend training sessions at the hospital, e.g. due to prolonged transport time, the remaining training sessions will be tailored individually at commercial training facilities near the patients’ own home. However, patients must attend at least one session per week supervised at the hospital training facility.

If patients, due to treatment side effects, are unable to attend at least one weekly training session, they will be given a leaflet describing two simple exercises (backward lunges and push-ups), and they will be encouraged to do the exercises (3 sets, 12 repetitions) every day until they are able to attend the supervised training again. Patients will fill in training logs during every session from which training adherence, changes in training volume, and intensity are reported.

No direct criteria for discontinuing the training program are provided, but if a patient feels incapable of training or if the physician, physiotherapist or training instructor deems the patient’s general condition not compatible with training, the program will be paused.

To support energy intake and mitigate negative energy balance on training days, patients are offered a meal and/or a protein supplement (e.g. Nutridrink compact (Nutricia), 125 mL, 1260 kJ, 12 g protein) immediately after training sessions. Patients in both groups are continuously screened (i.e. body weight assessments) by trained nurses ensuring the best possible energy intake to limit the risk of catabolic state during the CCRT and the approximately 6-week follow-up period immediately after.

### Controls

No restrictions on physical activity (PA) or other concomitant care are made for the control patients but no organized training will be offered to them. PA is reported in training logs. Except for blood sampling which, obviously, will not be drawn after any training session (see below) in the control group, there are no differences in tests and assessments between the groups.

### Study objectives and assessments

The primary endpoint is change in lean body mass (LBM). Secondary endpoints are training adherence and changes in and difference between groups in body composition, muscle strength, functional performance, weight, adverse events, dietary intake, self-reported PA, quality of life (QoL), labor market affiliation, blood biochemistry, cytokines in plasma, NK-cells in peripheral blood, sarcomeric protein content in muscles, as well as muscle fiber type and fiber size in muscle biopsies. See Table 3 for all assessment time points.

**Table 3 Tab3:**
[figure not shown]
Time schedule for study assessments

X marks when an examination is planned. XX marks at which time points blood samples are drawn both before and after a training session in the training group. Regarding week 13/14: Due to public holidays training can extend beyond 12 weeks, training continues until 36 sessions have been offered. Blood samples are drawn, weight registered and other examinations are performed after the 36 sessions. Abbreviations: ALT, alanine aminotransferase. ALP, alkaline phosphatase. e-GFR, estimated glomerular filtration rate. LDH, lactate dehydrogenase. HS-CRP, high-sensitive c-reactive protein. TSH, thyroid stimulating hormone. INR, international normalized ratio. DXA, dual-energy X-ray absorptiometry. Approx., approximately

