### Clinical outcomes

#### Body composition

The primary endpoint is change in lean body mass (LBM) which will be assessed after 12 weeks of PRT or control using Dual Energy X-ray Absorptiometry (DXA) (Herlev site: GE lunar iDXA, GE Healthcare Technologies; Aarhus site: Hologic QDR-series, Hologic Inc., Bedford, MA, USA). The hypothesis is that 12 weeks of progressive resistance training can attenuate the loss of LBM by at least 25%. This time span was chosen since 12 weeks are considered a sufficient period of PRT needed to affect LBM. Furthermore, this time point is a usual evaluating point for head and neck cancer as it coincide with the 2-month post-radiotherapy follow-up. Changes in total body mass and fat mass will also be assessed. Total body weight, with patients in light clothing and no shoes, will be measured weekly by the same digital scale at each site during therapy and bi-weekly thereafter.

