### Statistical considerations

The primary endpoint is difference in mean change of LBM between the training and the control group, specifically, whether attending this particular PRT program can significantly attenuate the loss of LBM after 12 weeks of PRT, which approximately aligns with the time where the treatment is evaluated (2 months after end of radiotherapy). Thus, the time at which the primary endpoint is evaluated is at 12 weeks after initiation of PRT.

The second important decision was to define a clinically meaningful endpoint in terms of difference in change in LBM loss. Of course, the 12 week period in which it was possible to train was included as a parameter since the short training period would influence the possible outcome, and even more so as patients were expected to lose LBM as a result of side effects to treatment. Limited clinical data were available on the possible effect of a 12-week PRT program on LBM change during concomitant chemoradiotherapy, though Lonbro et al. did find that head and neck cancer patients attending a 12-week PRT program initiated after radiotherapy gained an average of 2.3 kg (95% CI 1.7–3.0) [20]. A similar effect can probably not be expected when PRT is performed during chemoradiotherapy as the patients during this time are in a catabolic state. This was seen in our pilot study where patients despite PRT had a mean LBM loss of 3.6 kg ([name] et al., manuscript submitted).

Based on these deliberations we concluded that a difference of 25% in LBM loss between the exercise group and the control group (which, estimated from data in the pilot study, would be 1.2 kg of LBM in absolute difference) would be a clinically meaningful difference, and yet, an obtainable goal in the circumstance of undergoing CCRT.

Thus, the sample size calculation is based on changes in LBM in our one-armed pilot study where a 3.6 kg reduction (corresponding to 6.8%) in LBM was detected after 12 weeks of PRT ([name] et al., manuscript submitted). A priori, a sample size of 34 in each group will have 80% power to detect a difference in means of 25% ((9.06%–6.8%)/9.06%) between the two groups (corresponding to an estimated mean LBM loss of 6.80% from baseline in the training group and an estimated LBM loss of 9.06% in the control group with a standard deviation of 3.27). A two group t-test with a 0.05 two-sided significance level was used.

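### Primary DXA timing is fixed inconsistently (12 weeks versus after 36 offered sessions), so scan day can differ between the arms

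*Protocol article*

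**What the plan says.** Two sections of the protocol article give a fixed time for the primary scan. Statistical considerations states that "the time at which the primary endpoint is evaluated is at 12 weeks after initiation of PRT". Body composition says of the change in LBM: "which will be assessed after 12 weeks of PRT or control using Dual Energy X-ray Absorptiometry (DXA").

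The note to Table 3, the assessment schedule, gives a different trigger in its comment on week 13/14: "Due to public holidays training can extend beyond 12 weeks, training continues until 36 sessions have been offered". It continues: "Blood samples are drawn, weight registered and other examinations are performed after the 36 sessions". The Intervention section explains how the count can run late. If a session is cancelled for a treatment-related intervention, radiotherapy, a scan or a public holiday, "the session will be replaced at the end of the training program". There is a limit: "Sessions missed for personal reasons or incapacitation will not be substituted".

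Controls are offered no organized training. The Controls section says that, apart from post-training blood samples, "there are no differences in tests and assessments between the groups". It gives no rule on timing.

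Body composition also justifies week 12 on the ground that "it coincide with the 2-month post-radiotherapy follow-up".

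**The concern.** A fixed 12 weeks and a session count are different clocks. They agree only for a patient with no replaced sessions. Each replaced session moves the second clock later, and only training patients have sessions to replace. If the primary DXA is among the examinations that follow the 36 sessions, a training patient's scan waits for the make-up sessions. A control has nothing to wait for, and no rule shown moves the control's scan to match.

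The primary endpoint is a difference in change, and elapsed time is part of any change. If LBM is moving around weeks 12–14, a mean difference in scan day between the arms is added to the training effect or subtracted from it. Randomization does not protect against this, because the gap arises after allocation. Blinding of the DXA staff does not remove it either.

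**Working it through.** **The plan's own figure.** Statistical considerations gives expected losses of 6.80% and 9.06%, SD 3.27, two-sided alpha 0.05 and 80% power. The difference is 9.06 − 6.80 = 2.26 points. A two-sample t-test gives n = 33.85, so 34 per group, with power 0.802. With 5% dropout, 34/0.95 = 35.8, so 36 per group and 72 in total. The stated sample size reproduces.

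**Scale.** The pilot loss of 3.6 kg equals 6.8%, so mean baseline LBM is about 3.6/0.068 = 52.9 kg.

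**Length of the gap.** At three sessions a week, a mean delay of 1 week needs about three replaced sessions per training patient, and 2 weeks about six. The Table 3 note points to week 13/14, so 1–2 weeks is taken as the upper range. If only half the patients are delayed, the mean gap is half as long.

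**Slope.** The documents give no LBM slope at weeks 12–14. Three assumptions cover the range:
- flat: 0 points per week;
- recovery: the 2.3 kg gained in 12 weeks of training after radiotherapy (cited in Statistical considerations), 2.3/12 = 0.192 kg per week, or 0.192/52.9 = 0.36 points per week;
- continued loss: the training arm's expected average, 6.8/12 = 0.57 points per week.

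**Effect.** Shift b = mean gap × slope. SE = 3.27 × √(2/34) = 0.793. The rejection rate comes from the noncentral t with 66 df and noncentrality (δ + b)/0.793, where δ is 0 or 2.26.

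| Assumed slope | Mean gap (weeks) | Shift (points) | Share of 2.26 | Rejection, no true effect | Power, true 2.26 |
|---|---|---|---|---|---|
| Flat | any | 0 | 0% | 0.05 | 0.80 |
| Recovery 0.36 | 0.5 | +0.18 | 8% | 0.06 | 0.86 |
| Recovery 0.36 | 1 | +0.36 | 16% | 0.07 | 0.90 |
| Recovery 0.36 | 2 | +0.72 | 32% | 0.15 | 0.96 |
| Loss 0.57 | 0.5 | −0.28 | 13% | 0.06 | 0.69 |
| Loss 0.57 | 1 | −0.57 | 25% | 0.11 | 0.56 |
| Loss 0.57 | 2 | −1.13 | 50% | 0.29 | 0.29 |

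A positive shift favours training. Using the confidence limits of the cited gain (1.7 to 3.0 kg), the recovery slope is 0.27 to 0.47 points per week. The shift is then 12–21% of the target for 1 week and 24–42% for 2 weeks.

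**The 2-month statement.** 66–68 Gy in 2 Gy fractions is 33–34 fractions. At 6 per week that is 5.5–5.7 weeks. Adding two months (8.7 weeks) gives week 14.2–14.4, about two weeks after week 12.

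**The case against.** The strongest reply is that the article never says the arms are scanned at different times. The note does not mention DXA, the Table 3 grid is not shown, and the Controls section says assessments do not differ. Both arms may share the week 13/14 visit, and the full protocol may fix the window. This stands in part. A reader might infer that the session rule delays the training arm only, but that rests on the absence of a control rule, not on a statement. It does not dissolve the conflict. If both arms are scanned in week 13/14, the fixed 12 weeks is wrong; if controls are scanned at week 12, the arms differ.

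Other parts of the reply hold:
- A reader might say that controls have no 12-week clock. They do: training starts together with chemoradiotherapy, and Body composition speaks of 12 weeks of control.
- A reader might think the scan waits until 36 sessions are completed. The trigger is sessions offered, and personal or incapacity absences are not made up. This limits the delay and makes a 2-week mean gap an extreme case.
- A reader might count the 2-month visit as a third schedule. It is a reason given for choosing week 12, and it is hedged in Statistical considerations and in the Discussion. It applies to both arms alike.
- The recovery slope comes from patients who were training after radiotherapy, so it mixes training gain with the passage of time.

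**Conclusion.** The timing of the primary DXA is stated inconsistently, and the session trigger, followed literally, makes scan day depend on arm. The LBM contrast can therefore be biased. A reader might go further and conclude that it is biased, and in favour of training. The documents do not support that. Bias needs both a systematic mean gap and a non-zero slope at weeks 12–14, and neither is given.

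Under the assumptions shown, the effect of a 1–2 week mean gap runs from nothing, through a shift of 16–32% of the target towards training, to 25–50% of the target against it. These figures also rest on reading the end-of-training examinations as including DXA. The point is of moderate weight. It needs a clear correction, but it is not a demonstrated flaw in the result and has no bearing on the sample size.

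**What to change.** Reconcile the Table 3 note and the make-up rule with the Body composition and Statistical considerations sections:
- State one target day and one window for the primary DXA, the same in both arms, counted from the start of chemoradiotherapy (or from randomization) and independent of the number of sessions offered.
- Say explicitly whether the examinations in the Table 3 note include DXA, and how the rule applies to controls.
- Record the actual scan day and report its distribution by arm.
- Add a sensitivity analysis restricted to scans inside the window. Adjusting for scan day alone is a weaker remedy, because scan day arises after randomization and may be tied to arm.
- Correct the statement that week 12 coincides with the 2-month post-radiotherapy visit, which falls at about week 14.

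The cost is a few sentences. Some training patients will be scanned before their last make-up sessions, which slightly reduces the training dose reflected in the endpoint. The numbers stay at 34 evaluable and 36 enrolled per group. A timing gap cannot be fully repaired once the scans are done, so the window should be settled beforehand.
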